### Additional Analyses of Primary Outcome Measure

The mean change at the affected frequencies will be classified into the following categories:

| Definition* | Improvement                                                                                                                                                                                                          |
|-------------|----------------------------------------------------------------------------------------------------------------------------------------------------------------------------------------------------------------------|
| Recovery    | Hearing level recovers within 30 dB at 250, 500, 1000, 2000 Hz and within 25 dB at 4000 Hz, or
Hearing level recovers to that of contralateral intact ear if hearing in intact ear can be considered to be stable |
| Good        | Average hearing improvement for five frequencies $\geq 30$ dB                                                                                                                                                        |
| Fair        | Average hearing improvement for five frequencies $\geq 10$ and $\leq 30$ dB                                                                                                                                          |
| No change   | Average hearing improvement for five frequencies is within 10 dB                                                                                                                                                     |

\*Hearing recovery as defined by the Ad Hoc Committee of the Ministry of Health and Welfare in Japan

|                                |                             |                      |
|--------------------------------|-----------------------------|----------------------|
| Protocol Amendment 7.1         | Study no.: NM-V-101         | Page 58 of 85 |
| Date of Amendment: 15 Feb 2018 | EudraCT No.: 2012-000066-37 |                      |

A comparison of mean changes of participants who completed the study will be made. Multiple linear regression analysis will be performed to evaluate the magnitude of the treatment effects after adjustment for participant characteristics such as age, gender, duration of SSHL prior to treatment, and baseline degree of hearing loss. The response and characteristics of participants who do not complete treatment will be evaluated to assess the missing response pattern.

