### 3.5. Sample Size Determination

Sample size determination for this study is based on 2-sided t-tests with a global alpha level of 5 % and a statistical power of 90 %. A standard deviation of 20 dB for the test statistic is assumed. In order to be able to confirm a treatment difference of 15 dB PTA of active treatment versus placebo with a 2:1 randomization, a total number of 87 evaluable patients will be required, 58 patients in the group receiving ancrod, and 29 patients receiving placebo. To compensate for dropouts, a total number of 99 patients is planned to be enrolled, 66 patients receiving ancrod, and 33 patients receiving placebo.

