### 6.1. Population Overview

Frequency tables will be prepared presenting the number of patients randomized, eligible (i.e., meeting all inclusion criteria but none of the exclusion criteria), and treated. Moreover, the following information will be given for all patients randomized:

- The date of the FPI (date of informed consent)
- The date of first patient's first IMP intake
- The date of last patient's last treatment
- The date of the LPO (date of last documented visit).

Reasons for exclusion from any analysis population will be shown in a patient data listing.

For all patients randomized, the following information will be summarized in a frequency table:

- The number and percentage of patients completing the trial [1] and of those who terminated the trial prematurely ('Dropouts')
- The number of patients with unblinding performed
- The number of patients per study center
- The patient disposition by visit (attended/missed).

[1] 'Completers' are patients with the answer 'Yes' to the question 'Regular end of observation?' on the CRF's End of Study form.

The reason for leaving the study (applies to dropouts only) will be given in a patient data listing.

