$$\text{Change in PTA} = \text{treatment} + \text{center} + \text{PTA at Visit 1.}$$

Underlying assumptions, such as normality and homogeneity of variance, are assessed at the BDRM. Should these assumptions be violated, appropriate data transformations or the choice of a non-parametric analysis method will be considered.

In addition, the mean change at the affected frequencies will be classified into the following categories and evaluated in a frequency table using the Freeman-Halton test:

| Definition* | Improvement                                                                                                                                                                                                            |
|-------------|------------------------------------------------------------------------------------------------------------------------------------------------------------------------------------------------------------------------|
| Recovery    | Hearing level recovers within 30 dB at 250, 500, 1000, 2000 Hz and within 25 dB at 4000 Hz, or
Hearing level recovers to that of contralateral intact ear if hearing in intact ear can be considered to be stable** |
| Good        | Average hearing improvement for the five frequencies $\geq 30$ dB                                                                                                                                                      |

|           |                                                                                 |
|-----------|---------------------------------------------------------------------------------|
| Fair      | Average hearing improvement for the five frequencies $\geq 10$ and $\leq 30$ dB |
| No change | Average hearing improvement for the five frequencies is within 10 dB            |

\* Hearing recovery as defined by the Ad Hoc Committee of the Ministry of Health and Welfare in Japan

\*\* The contralateral intact ear is regarded as stable when threshold values for Visit 1 and Visit 5 differ at most by 10 dB.

Besides, a comparison of mean changes of participants who completed the study will be made: Multiple linear regression analysis will be performed to evaluate the magnitude of the treatment effects after adjustment for participant characteristics such as age, duration of SSHL prior to treatment, and baseline degree of hearing loss (mild  $\leq 30$  dB; moderate to profound  $> 30$  dB).

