| Table 14.2.1.4  | Multiple Linear Regression on Change in PTA Air from Screening to Day 8                | FAS, PPS            |
| Table 14.2.1.5  | Change in PTA Air from Screening to Day 8 by Subgroups                                 | FAS                 |
| Table 14.2.1.6  | Step-Down ANCOVA on Change in PTA Air from Screening to Day 8 to Identify Risk Factors | FAS                 |
| Table 14.2.2.1  | Change in PTA Air from Screening to Day 30                                             | FAS, PPS            |
| Table 14.2.2.2  | Change in PTA Air from Screening to Day 90                                             | FAS, PPS            |
| Table 14.2.2.3  | Pure Tone Audiogram (PTA Bone) Values over Time                                        | FAS, PPS            |
| Table 14.2.2.4  | Change in PTA Bone from Screening to Day 8                                             | FAS, PPS            |
| Table 14.2.2.5  | Change in PTA Bone from Screening to Day 30                                            | FAS, PPS            |
| Table 14.2.2.6  | Change in PTA Bone from Screening to Day 90                                            | FAS, PPS            |
| Table 14.2.3.1  | Word Recognition Scores over Time                                                      | FAS, PPS            |
| Table 14.2.3.2  | Change in Word Recognition Score from Screening to Day 8                               | FAS, PPS            |
| Table 14.2.3.3  | Change in Word Recognition Score from Screening to Day 30                              | FAS, PPS            |
| Table 14.2.3.4  | Change in Word Recognition Score from Screening to Day 90                              | FAS, PPS            |
| Table 14.2.4.1  | Fibrinogen Values over Time                                                            | FAS                 |
| Table 14.2.4.2  | Change in Fibrinogen from Screening to Day 2                                           | FAS                 |
| Table 14.2.4.3  | Change in Fibrinogen from Screening to Day 8                                           | FAS                 |
| Table 14.2.5.1  | Biomarker Values over Time                                                             | FAS                 |
| Table 14.2.5.2  | Change in Biomarkers from Screening to Day 8                                           | FAS                 |
| Table 14.2.5.3  | Correlation of Biomarkers with Clinical Effects                                        | FAS                 |

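### The supplementary Day 8 regression in SAP 9.1.1 cuts baseline hearing at 30 dB, and its population is completers in the text but FAS and PPS in the table list

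*Combined protocol and SAP*

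**What the plan says.** Protocol 10.2.1 (Additional Analyses of Primary Outcome Measure) plans two things in separate sentences: a comparison of mean changes among completers, and a multiple linear regression. The regression adjusts for characteristics such as "age, gender, duration of SSHL prior to treatment, and baseline degree of hearing loss". The protocol gives no cut-point for the degree of hearing loss.

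SAP 9.1.1 joins the two. It says that "a comparison of mean changes of participants who completed the study will be made" and then, after a colon, describes the regression, with "adjustment for participant characteristics such as age, duration of SSHL prior to treatment, and baseline degree of hearing loss (mild" up to 30 dB; moderate to profound above 30 dB). Gender is not named.

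SAP 6.1 explains that completers "are patients with the answer 'Yes' to the question 'Regular end of observation", a question on the End of Study form. Protocol 4.4 makes Day 90 the final visit.

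SAP 13.2 lists the output, Table 14.2.1.4, as "Multiple Linear Regression on Change in PTA Air from Screening to Day 8" and assigns it to the FAS and PPS. SAP 5.3 states that the FAS contains dropouts.

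The main model in SAP 9.1.1 uses PTA at Visit 1 as a covariate, and SAP Section 2 gives the reason: the change may depend on the baseline value.

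**The concern.** The regression is meant to show the size of the treatment effect after adjustment. Two features work against that.

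First, SAP Section 2 treats baseline as a likely predictor of change, yet this model keeps only which side of 30 dB a patient falls on. The rest of the baseline information goes into residual variance.

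Second, if the completer wording is followed, patients with a valid Day 8 audiogram can be left out because of what happened between Day 8 and Day 90. Missing data do not force this, because SAP 5.3 fills a missing Visit 5 value by carrying the baseline value forward. If the table list is followed, these patients stay in. A programmer cannot tell which is intended, and SAP 13.7 says that no table shells will be made.

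The cut, the completer link and the absence of gender are not among the departures listed in SAP Section 2. SAP 9.3 declares only the PPS and extra subgroup analyses as additions to the protocol.

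**Working it through.** **The plan's own figure.** The plan states no figure for this regression, so its sample size sets the scale. The inputs in SAP 3.5 are a two-sided 5% level, 90% power, a 15 dB difference and 2:1 allocation. On the spread it says: "A standard deviation of 20 dB for the test statistic is assumed".

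Placebo n = (1 + 1/2) × (1.960 + 1.282)² × (20/15)² = 28.02, rounded up to 29. With 58 on ancrod the total is 87, and 87/0.88 = 98.9, or 99 enrolled. Both stated figures reproduce.

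**Precision lost to the cut.** Let p be the share at or below 30 dB and r the correlation of baseline PTA with the Day 8 change. Neither is in the documents; I take p from 5% to 50% and r = 0.3, 0.5 and 0.7. I also assume a normal baseline, linearly related to change.

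- Share of the explained variance kept by two classes: k = φ(z_p)²/[p(1 − p)].
- Residual variance relative to the unadjusted variance: 1 − r² with continuous baseline, 1 − k r² with the cut.
- Ratio of standard errors (SE): √[(1 − k r²)/(1 − r²)].

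| p | k | SE ratio, r = 0.3 | r = 0.5 | r = 0.7 |
|---|---|---|---|---|
| 5% | 0.224 | 1.038 | 1.122 | 1.321 |
| 10% | 0.342 | 1.032 | 1.104 | 1.277 |
| 20% | 0.490 | 1.025 | 1.082 | 1.221 |
| 50% | 0.637 | 1.018 | 1.059 | 1.162 |

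Example, p = 5% and r = 0.5: (1 − 0.224 × 0.25)/(1 − 0.25) = 0.944/0.75 = 1.259, and √1.259 = 1.122. To match continuous adjustment on 87 patients, the two-class model would need 87 × 1.259 = 110. At p = 50% it would need 87 × 1.121 = 98.

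**At the enrolment now expected.** SAP Section 2 expects only a few more than 30 evaluable patients. Assume 36 (24 ancrod, 12 placebo), r = 0.5, and 20 dB as the unadjusted SD of the change. The residual SD is 20 × √0.75 = 17.3 dB with continuous baseline and 18.3 to 19.4 dB with the cut. The SE is the residual SD × √(1/12 + 1/24), or residual SD × 0.354. Normal-approximation power at 15 dB is 0.69 with continuous baseline and 0.59 to 0.64 with the cut. A 5% to 10% mild class would be 2 to 4 patients over both arms.

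**Completer selection.** This was simulated with 2 million patients per setting, SD 20 dB, 12% leaving (the SAP 5.3 dropout rate, here all placed after Day 8), and the odds of leaving changing by a factor of 1.65 or 2.7 per SD of the Day 8 change. Entries are the completers' treatment difference in favour of ancrod.

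| Who tends to leave | True effect 0 dB | True effect 15 dB |
|---|---|---|
| Poor results, both arms alike | 0 | 14.7 to 13.9 |
| Poor results, placebo only | −1.2 to −2.6 | 13.7 to 12.0 |
| Poor results on ancrod, good results on placebo | +2.2 to +4.3 | 17.1 to 18.9 |

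If leaving does not depend on the Day 8 result, there is no bias. Losing 12% of patients then only raises the SE by √(99/87) = 1.07.

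**The case against.** The strongest reply is that little hangs on this analysis. The protocol files it under additional analyses. The only confirmatory test is the FAS ANCOVA, which has neither the cut nor the completer restriction. That stands, and it sets the severity.

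A second reply is that the completer restriction may be only loose punctuation. The protocol keeps the two sentences apart, SAP 9 bases the primary analysis of efficacy variables on the FAS, SAP 9.1.2 repeats 9.1.1 on the PPS, and the table list agrees. That also stands in part: the documents show a conflict over the population and do not establish that selection will happen. The conflict still has to be resolved.

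A third reply is that two classes match the protocol's word 'degree' and the Degree of SSHL subgroup in SAP 4.2. This explains the choice. It does not recover the lost precision, and the subgroup tables can keep the cut.

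Readers might infer more than the documents support:

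- *That gender is dropped.* Both lists open with 'such as' and exclude nothing. Gender is also a subgroup and a starting term of the step-down ANCOVA in SAP 5.7. No precision cost of omitting it can be shown.
- *That this is the only estimate adjusted beyond baseline and centre.* The step-down ANCOVA is another adjusted model, although its stated aim is risk factors.
- *That the mild class must be tiny.* An affected frequency is at least 20 dB worse than the other ear, so it exceeds 30 dB wherever the other ear is above 10 dB. But SAP 4.2 counts 25 dB or better as normal, which allows 10 dB or less, and included non-affected frequencies can lower the mean.
- *That rescue decides who counts.* Rescue after Day 8 is permitted and does not make a patient a non-completer.
- *That about 12 of 99 patients are lost to later events.* The 12% is not split by time and includes dropout before Day 8. At an assumed 36 patients it is about 4.

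**Conclusion.** The point holds as a low-severity, free improvement. The cut at 30 dB costs precision whenever baseline predicts change linearly. The cost is slight at r = 0.3 (SE up about 2-4%), moderate at r = 0.5 (6-12%) and substantial only at r = 0.7 (16-32%). These ranges rest on a normal baseline and an assumed 5% to 50% of patients at or below 30 dB.

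The population is contradictory within the SAP. Following the text would condition a Day 8 comparison on later events. Protocol 3.1 lets non-improvers switch treatment after Day 8, and protocol 5.1.4 lets the investigator withdraw a patient thought not to be appropriately treated. Dropout related to the Day 8 result is therefore plausible, but nothing in the documents shows it, so neither the sign nor the size of a bias can be stated. The confirmatory conclusion does not change.

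**What to change.** In SAP 9.1.1:

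- Enter baseline PTA as a continuous covariate in the regression.
- Separate the regression from the completer sentence. Run it on the FAS with the PPS repeat that Table 14.2.1.4 already lists.
- If a completer comparison is wanted, keep it as a labelled sensitivity analysis.
- Replace 'such as' with a closed covariate list, and include gender because the protocol names it.
- Record in SAP Section 2 any departure from the protocol that remains.

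The cost is SAP wording, to be settled before unblinding. All the variables are already collected, and the table list needs no change unless a completer table is added.

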### 9.1.2. Supportive and Sensitivity Analyses

As a sensitivity analysis, the statistical evaluation as shown in Section 9.1.1 will be repeated for the PPS.

## 9.2. Analyses of Secondary Efficacy Variables

For secondary efficacy variables (except for fibrinogen) also, LOCF imputation will be done for missing post-baseline values up to Visit 5.

### 9.2.1. Change in PTA (Air) from Visit 1 to Day 30 and Day 90

The change in PTA (Air) in the affected ear from Visit 1 to Day 30 (Visit 6) and Day 90 (Visit 7) is a secondary efficacy variable. The statistical analysis will be conducted for the FAS and the PPS in analogy to the primary efficacy variable, excluding the categorical analysis, the multiple linear regression, and the subgroup analyses.

### 9.2.2. Change in PTA (Bone) from Visit 1 to Day 8, Day 30 and Day 90

For PTA (Bone), the definition of the affected frequencies and the computation of the PTA summary value per visit will be based on the bone-conducted thresholds in the same manner as described above for PTA (Air). The statistical analysis of the changes in PTA (Bone) will be conducted for the FAS and the PPS in analogy to the primary efficacy variable, excluding the categorical analysis, the multiple linear regression, and the subgroup analyses.

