## **10**      **Statistics**

### **10.1**      **Sample Size Determination**

Sample size determination for this study is based on 2-sided t-tests with a global alpha level of 5% and a statistical power of 90%. A standard deviation of 20 dB for the test statistic is assumed. In order to be able to confirm a treatment difference of 15 dB PTA of active treatment versus placebo with a 2:1 randomization, a total number of 87 evaluable patients will be required, 58 patients in the group receiving ancrod, and 29 patients receiving placebo. To compensate for dropouts, a total number of 99 patients is planned to be enrolled, 66 patients receiving ancrod, and 33 patients receiving placebo.

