#### 5.3. Handling of Dropouts and Missing Data

A screening failure is a patient having signed informed consent but discontinuing before being randomized. Such patients are not kept in the database.

Dropout patients are not explicitly referenced in the study protocol. However, the following definition is provided in this SAP:

- Patients randomized who either discontinue the study prematurely or are withdrawn from study by the investigator before the planned study termination are assessed as **dropouts**.

Dropout patients are not substituted. To compensate for dropouts, a 12 % dropout rate was used in the sample size determination.

Dropout patients will be evaluated like any other patient terminating the study regularly while accounting for missing data. The FAS includes dropout patients.

Missing values will usually be shown as missing in patient data listings. If there is the need to show data imputations, imputed values are flagged appropriately.

For the statistical analysis of efficacy variables, the LOCF (last observation carried forward) method will be applied to impute missing Visit 5 values, i.e, the baseline value will be carried forward. Missing values for Visit 6 or Visit 7 will not be replaced as these visits are far beyond treatment stop.

Regarding PTA, a missing PTA threshold value for a given frequency at Visit 5 is replaced by the respective preceding value available at Screening. Imputations will not use values of the other ear (left/right) or of the other conduction type (air/bone). If a baseline value for a given frequency is missing, the frequency will be excluded from statistical analysis of the respective patient.

Regarding the statistical evaluation of background and safety variables, missing values will not be replaced or imputed; they will be handled as missing by displaying an own category in frequency tables.

However, missing data, outliers and other spurious or implausible data are discussed in the BDRM prior to unblinding the database.

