#### 9.2.5. Biomarkers

The following biomarkers are determined at Screening (Visit 1) and Day 8 (Visit 5) in venous blood samples as surrogate parameters for efficacy:

- Inflammatory markers: interleukin-6, TNF- $\alpha$
- Molecular markers of leucocyte activation: CD38+, CD40+ cells.

The change in biomarkers from Screening to Day 8 will be analyzed for the FAS in analogy to the primary efficacy variable, excluding the categorical analysis, the multiple linear regression, and the subgroup analyses.

Moreover, the inflammatory and cellular markers' relative change at Visit 5 will be correlated (Spearman's correlation coefficient) with the following effects:

- PTA (Air) absolute change at Visit 5
- Fibrinogen relative change at Visit 5.

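### Carrying baseline forward for both biomarkers and PTA puts artificial (0 %, 0 dB) pairs into the Visit 5 biomarker-PTA correlation, which can bias the coefficient in either direction

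*Combined protocol and SAP*

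**What the plan says.** The rule has to be assembled from several places.

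- SAP 3.4.2 lists biomarker change from Screening to Day 8 as a secondary efficacy variable.
- SAP 4.3, which defines absolute and relative change, opens by applying the imputation rules of 5.3 whenever a target-visit value is unavailable.
- SAP 5.3 fills a missing Visit 5 efficacy value with the baseline value, and a missing Visit 5 PTA threshold with the Screening threshold. It also states that the FAS includes dropouts.
- SAP 9.2 says of secondary efficacy variables, with fibrinogen as the only exception, that "LOCF imputation will be done for missing post-baseline values up to Visit 5".
- SAP 9.2.5 says that "the inflammatory and cellular markers' relative change at Visit 5 will be correlated (Spearman's correlation coefficient") with two effects: the absolute PTA (Air) change and the relative fibrinogen change, both at Visit 5.
- SAP 13.2 assigns the correlation table (14.2.5.3) to the FAS only. Biomarkers are not among the variables that SAP 9 repeats in the PPS.

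No sentence states that imputed values enter the correlation, and none keeps them out. Read together, the sections put them in.

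**The concern.** The relationship between biomarkers and clinical efficacy is a declared secondary objective (Protocol 3.2, SAP 3.1), and this correlation is its direct analysis. A FAS patient with baseline values but no Visit 5 value of either variable contributes a 0 % marker change and a 0 dB PTA change. Several such patients form a tied block at one point. If the observed pairs lie mostly to one side of zero on both axes, the gap between block and observed pairs registers as association, although it reflects only who missed the visit. Depending on the signs, it can suggest a link that does not exist or hide one that does.

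No planned output would expose this: there is no observed-pairs version and no PPS repeat. The marker-fibrinogen correlation, in the same table, does not fill fibrinogen. The two coefficients can therefore rest on different patients without the table saying so.

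**Working it through.** **Inputs from the documents**

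- Protocol 10.1: "A standard deviation of 20 dB for the test statistic is assumed", and the aim is to "confirm a treatment difference of 15 dB PTA of active treatment versus placebo with a 2:1 randomization". So 15/20 = 0.75 SD between arms.
- SAP 3.5: "a total number of 87 evaluable patients will be required, 58 patients in the group receiving ancrod, and 29 patients receiving placebo".
- SAP 5.3: "To compensate for dropouts, a 12 % dropout rate was used in the sample size determination".
- SAP 2: only a few more evaluable patients are expected than the 30 planned for the interim analysis. I take n = 34 as an assumption.
- SAP 9: efficacy tables are by treatment group, not overall. At 2:1, 34 patients give about 23 on ancrod and 11 on placebo.

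**The plan's own figures reproduce.** Placebo n = 1.5 × (1.960 + 1.282)² × (20/15)² = 28.02, rounded up to 29. With 58 on ancrod the total is 87, and exact t-test power is 90.3 %. Then 87/0.88 = 98.9, which gives 99.

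**Size of the bias.** The documents give no figure for the correlation, so I derived one. Let p be the filled share, and a and b the shares of observed marker and PTA changes below zero. Assume the observed changes are truly independent. On a 0-to-1 rank scale:

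- the tied block sits (1 − p)(a − ½) and (1 − p)(b − ½) from the middle on the two axes;
- the observed patients sit on average −p(a − ½) and −p(b − ½) from it;
- the rank covariance is therefore p(1 − p)(a − ½)(b − ½);
- the rank variance with a tied share p is (1 − p³)/12.

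Hence spurious rho = 12 p(1 − p)(a − ½)(b − ½)/(1 − p³).

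If either share is one half, rho is zero. If the two changes run in opposite directions, rho is negative. For p = 0.12 and normal changes with means 0.75 and 1.0 SD in the same direction, a = 0.773 and b = 0.841. Then rho = 12 × 0.12 × 0.88 × 0.273 × 0.341/0.998 = 0.118, or about 0.12.

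**Simulation.** Independent normal changes, k patients set to (0, 0), two-sided 5 % Spearman test, 2,000 to 4,000 data sets per row:

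| n | k | Mean changes (SD) | Mean rho | Rejection |
|---|---|---|---|---|
| 99 | 12 | 0 and 0 | 0.00 | 7 % |
| 99 | 12 | 0.75 and 0 | 0.00 | 6 % |
| 99 | 12 | 0.75 and 0.5, same sign | 0.07 | 11 % |
| 99 | 12 | 0.75 and 0.5, opposite signs | −0.07 | 11 % |
| 99 | 12 | 0.75 and 1.0, same sign | 0.12 | 22 % |
| 99 | 12 | 1.0 and 1.0, same sign | 0.15 | 31 % |
| 34 | 4 | 0.75 and 0.5, same sign | 0.07 | 6 % |
| 34 | 4 | 0.75 and 1.0, same sign | 0.12 | 9 % |
| 34 | 4 | 1.0 and 1.0, same sign | 0.14 | 12 % |
| 34 | 2 | 1.0 and 1.0, same sign | 0.08 | 7 % |
| 22 | 2 | 0.75 and 1.0, same sign | 0.09 | 6 % |
| 22 | 1 | 0.75 and 1.0, same sign | 0.05 | 5 % |

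With observed pairs only, mean rho is about 0 and rejection is 4 to 6 % throughout.

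**When a real correlation exists.** Take a true correlation of 0.4 (Spearman 0.38 on observed pairs), n = 99, k = 12 and mean changes of 0.5 and 0.75 SD. Filling both variables gives 0.28 if the changes run in opposite directions and 0.41 if they run in the same direction. If only the marker is missing and filled, rho falls to about 0.35. That weakens a link and creates none.

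**The case against.** The strongest case against is that little of this will show in the trial as it now stands, and most of that argument holds.

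- **Size.** SAP 2 no longer expects 99 patients, and SAP 9 presents results by arm. The 22 % figure belongs to the original plan. At 22 to 34 patients with one or two filled, rejection is close to nominal.
- **The 12 %.** It covers dropout over the whole study to Day 90, not a missing Day 8 visit. Protocol 4.5 asks for a full final examination at withdrawal, as in Section 4.2, whose Day 8 list includes audiometry and biomarkers. Neither document says whether those values count as Visit 5.
- **Expected changes.** No marker change is stated anywhere. The 0.75 SD concerns PTA only, and describes the ancrod mean (as a minimum) only if placebo does not worsen.
- **No test.** SAP 9.2.5 names a coefficient, not a p-value, and SAP 9 makes all secondary analyses exploratory.

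These points limit the size and weight of the problem. They do not remove it, because the coefficient itself is biased whether or not it is tested.

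A reader might infer more than the documents support:

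- That the fill always manufactures a correlation. It does not if either change is centred on zero.
- That every patient without a Day 8 visit enters as (0, 0). A missing or zero marker baseline gives no relative change (SAP 4.3), and withdrawal values may exist.
- That all four markers would be pushed the same way. Each follows the sign of its own mean change.
- That the marker-fibrinogen correlation has the same fault. Fibrinogen is not filled, so joint zeros do not arise there.

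**Conclusion.** The point holds in conditional form and is minor. The SAP as written admits artificial (0 %, 0 dB) pairs to the biomarker-PTA correlation. They bias rho only when both typical changes differ from zero, in a direction set by the two signs.

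With 12 % jointly missing and mean changes of 0.75 and 1.0 SD, the spurious rho is about 0.12 in absolute value. Rejection would be about 9 % at n = 34 and 22 % at n = 99, against about 5 % with observed pairs. With one or two filled patients among 22 to 34, rho shifts by about 0.03 to 0.10 and rejection stays near 5 to 7 %.

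These figures assume normal changes that are independent of each other and of missingness. The mean changes, n = 34 and the filled share at Day 8 are also assumptions. The documents do not support a claim that a false biomarker signal is likely. They do support closing the gap, because values nobody measured should not shape the direct analysis of a stated objective.

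**What to change.** In SAP 9.2.5, state that the biomarker-PTA and biomarker-fibrinogen correlations use only patients with observed, non-imputed Visit 1 and Visit 5 values of both variables. Both coefficients for a marker then follow one rule, and the number of pairs should be printed beside each. Any version with carried-forward values should appear only as a sensitivity analysis. The same sentence can say whether examination values taken at early withdrawal count as Visit 5 values.

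Leave the LOCF rule for the between-arm biomarker comparison as it is; this point does not bear on it.

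The cost is a sentence or two in the SAP and one filter in the program. The downside is a few fewer pairs, and the pairs lost to joint filling carry no information on the relationship.
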